**Additional Measurements**

Immediately after the intervention activity (or baseline for those who are randomized to branch 1), participants will be asked to complete a brief intentions survey (Appendix F). These questions will focus on HIV disclosure, condom use, alcohol/drug use, and HIV testing (for those who are HIV-negative) in the next 60 days.

Additionally, we will also record the number and categories of link “clicks” that consented respondents make when shown the resource page after completing the post-intervention assessment (baseline) and after completing the follow-up assessment. This page, found in Appendix G, contains links to a variety of health related resources. The data will be automatically added to the individual participant’s data file.

**Outcomes and Minimum Meaningful Differences**

The primary outcomes are increases in HIV serostatus disclosure, HIV testing, and condom use between baseline and 60-days follow-up. Although we will be comparing within and across all branches, we expect the greatest differences to be found between control branch 1 and branch 5 (both videos) for the primary outcomes. A minimal meaningful difference for the primary outcomes will be to detect statistical significance in behavior change between baseline and follow-up at both the 0.01 and 0.05 alpha levels.

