**Intended/Potential Use of the Study Findings**

A recent study comparing the cost-effectiveness of HIV prevention interventions found that the two most important factors that determined cost-effectiveness were the HIV prevalence of the target population and the cost per person reached.30 In fact, one of the two most cost-effective interventions overall was showing videos in STI clinics (individual-level).30 These findings support our proposed online behavioral intervention using video vignettes in terms of cost-effectiveness and reaching high-risk MSM. If successful, this type of novel Internet-based intervention approach will be efficient, cost-effective, feasible to replicate, and especially useful in reaching men in rural areas or other hard-to-reach populations.

Specific Aims and Hypotheses

**Aim 1:** To test the feasibility of implementing an innovative national online randomized controlled, multi-branched, behavioral intervention for men who have reportedoral or anal sex with any male (new partner or not) in the past 60 days AND reported oral, anal or vaginal sex for the first time (new partner) with a male or female within the past 60 days.

**Aim 2:** a) To identify and recruit men who have sex with men met online or offline, and who, in the last 60 days, met a new sex partner; b) To enroll and randomly assign 3,000 MSM, representing diverse race/ethnicities and geography, into one control or four intervention conditions; c) To maximize retention 60-days post-intervention to complete the follow-up survey.

**Aim 3:** To evaluate the intervention conditions by comparing outcome risk measures (HIV disclosure, HIV testing, condom use, drug and/or alcohol use before sex, and depressive and/or anxiety symptomatology) at 2 time points for 5 study conditions.

**Aim 3 Primary Hypotheses:** Between baseline and 60-day follow-up there will be an increase in the following: a) HIV disclosure with new sex partners, b) HIV testing, and c) condom use in intervention branches 3, 4, and 5, compared to branches 1 and 2.

**Aim 3 Secondary Hypotheses:** Between baseline and follow-up, there will be a decrease in the following: a) drug use before sex, b) alcohol use before sex, and c) depressive and/or anxiety symptomatology in intervention branches 3, 4, and 5, compared to branches 1 and 2.

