**Evaluation of Branches**

Participants in all branches will be scheduled to complete three quantitative surveys including a baseline assessment, a brief immediate post-intervention assessment (or immediate post-baseline assessment for the control group) measuring intent to change behavior during the next 60 days, and a 60-day follow-up assessment. Additionally, we will record the number of “clicks” on the resources webpage (presented after the post-intervention assessment) which represent intent to access health services and information. Our 5-branch design will allow us to directly compare, within and across branch, changes in primary and secondary outcome behaviors from baseline to 60 days follow-up. By doing so, we will be able to measure the efficacy of each of the study branches, as compared to the control branch and standard text-based prevention branch and relative to each other. The multi-branch design will allow us to directly compare the video-based interventions to the text-based prevention web-page to determine which branch elicits the most significant change in behavior.

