**DATA HANDLING AND ANALYSIS**

Although no personally identifying information other than email addresses (which will be encrypted and stored separately), will be collected at any point during the surveys, several technical steps will be taken to ensure the security and privacy of data in general. All survey data will be stored on a secure Public Health Solutions web server with firewalls and industry standard protections and will be removed from the web server at the end of the survey period.

All analyses will be performed in SPSS 14.0 and SAS 9.1 for Windows. For the overall sample (3,000) we will use a reduced alpha level (.01) as a criterion for statistical significance. For the within-branch analyses (n=600 or less) we will use the conventional alpha level (.05). Due to decreased power, all interaction tests will be conducted at the 0.10 level of significance.

The first analytic procedure will be to use ANOVA or chi-square to compare key characteristics (i.e., age, race/ethnicity, income) among and between the 5 randomized groups to ensure that there are no statistical differences, and to verify that computerized randomization worked.

**Frequency Distributions**: Frequency distributions will be produced for all variables and be used to describe the sample characteristics and answer key questions (e.g., what percentage of men reported unprotected anal or vaginal intercourse in their last sexual encounter with a new male or female partner?).

**Bivariate Analysis:** Bivariate analysis will be conducted to identify measures that show significant associations with primary outcome variables, (e.g., asking or telling HIV status to new sex partners [yes/no], HIV testing during the 60 days after baseline [y/n], and unprotected anal or vaginal intercourse [y/n]). Associations between measures with more than two values (e.g., drug use increased, decreased, or remained the same) and binary outcomes (e.g., HIV/STI testing [y/n]) will be tested, though the Pearson Chi-Square test and t-tests will be performed with continuous variables (e.g., number of sex partners in past 60 days).

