**Multivariate Analysis:** For dichotomous outcomes, we will use logistic regression models to simultaneously examine the effects of predictors found to have a statistically significant association with the binary outcomes in bivariate analyses. Further, logistic regression will allow the introduction of the pretest observation (e.g. asked new partner’s HIV status) and treatment status as predictors and a set of demographic control variables. For continuous outcomes, we will use linear regression models to study quantitative outcome variables such as number of days respondent drank alcohol in the past 60 days (at baseline and 60-day follow-up).

**Analysis of Treatment Branches:** For analysis of within-treatment branches, we will use McNemar’s Test, which is a chi-square test used when data consist of paired observations on a particular outcome (i.e., pre-post treatment design), such as HIV disclosure with a new sex partner. For analysis of between-treatment branches, we will test differences across interventions or group mean differences by employing linear regression with interaction terms. We will also use ANOVA to examine within- and across-branch differences between those who complete the intervention activities and those who do not.

**Safeguarding against Confounding:** To safeguard against confounding in the multivariate logistic regression models, variables not significantly associated with outcomes in simple bivariate analyses may be included for conventional demographic items or if it is highly plausible (either biologically or behaviorally) that they are associated with the outcome.

**Interactions:** Tests for interactions will be conducted between pairs of explanatory factors and binary outcomes to assess possible interactions.

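### The minimal meaningful difference is defined as statistical significance of change from baseline, with no size and no comparator, which conflicts with the between-branch hypothesis and power calculation

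*Protocol*

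**What the plan says.** Outcomes and Minimum Meaningful Differences words the endpoints as change over time: "The primary outcomes are increases in HIV serostatus disclosure, HIV testing, and condom use between baseline and 60-days follow-up". It continues: "Although we will be comparing within and across all branches, we expect the greatest differences to be found between control branch 1 and branch 5". It then sets the criterion: "A minimal meaningful difference for the primary outcomes will be to detect statistical significance in behavior change between baseline and follow-up". Two significance thresholds, 0.01 and 0.05, are attached to it. That section gives no number of percentage points or scale units, and the criterion sentence names no comparator branch.

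Other sections bear on how the sentence is read:

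- **Specific Aims and Hypotheses (Aim 3, primary).** The hypotheses are comparative and end with "condom use in intervention branches 3, 4, and 5, compared to branches 1 and 2".
- **Sampling, Sample Size, and Statistical Power.** The power table is for differences between two branches, with two-sided 0.05 divided over 10 pairwise comparisons.
- **Data Handling and Analysis.** "For the within-branch analyses (n=600 or less) we will use the conventional alpha level (.05"). The overall sample is tested at 0.01 and interactions at 0.10. Within-branch analysis uses McNemar's test, "which is a chi-square test used when data consist of paired observations on a particular outcome (i.e., pre-post treatment design"). Between-branch analysis uses linear regression with interaction terms.
- **Evaluation of Branches.** The videos are to be compared with the text page "to determine which branch elicits the most significant change in behavior".

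**The concern.** Statistical significance is not a difference. A minimal meaningful difference should say how large an effect matters, and in a randomised trial it should be an effect relative to a comparator. This criterion does neither, and it attaches two alpha levels without saying which one decides.

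The two levels are those that Data Handling and Analysis gives to the overall sample (0.01) and to within-branch analyses (0.05). Neither is the between-branch level of 0.005 used for the power table. The trial is therefore sized for one criterion, while its meaningful result is defined by another.

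If the sentence is applied branch by branch, change shared by all branches can satisfy it. Such change is plausible: every branch takes the same survey at baseline and follow-up, answers the intentions questions and sees the same resource page. A pattern of significance in a video branch but not in control could then be mistaken for a video effect, although it does not test the primary hypothesis.

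**Working it through.** **1. What the plan's own power refers to.** Inputs from the power table: 0.20 v 0.30 and alpha 0.05/10 = 0.005, two-sided. The formula is the normal approximation with continuity correction:

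power = Φ{[|p1 − p2| − 1/n − z·√(2p̄(1 − p̄)/n)] / √[(p1(1 − p1) + p2(1 − p2))/n]}

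For n = 300, 400, 500 and 600 it gives 0.471, 0.648, 0.781 and 0.872. The table states 0.476, 0.652, 0.784 and 0.874. Every cell of the table agrees within 0.013. The stated power is therefore for between-branch differences at 0.005 and says nothing about the pre-post criterion.

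**2. Inputs for the pre-post criterion.** Attrition and Retention Efforts gives 600 − 240 = 360 followed up in each of branches 1 and 2, and 600 − 180 = 420 in each of branches 3 to 5. The test is McNemar at 0.05, counted only when the change is an increase. Assumed, because the documents give no data on an untreated group: the same change in every branch, no video effect, and within-man correlation 0.4.

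**3. One case in full: 30% to 35% in every branch.**

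- Positive both times: 0.30 × 0.35 + 0.4 × √(0.30 × 0.70 × 0.35 × 0.65) = 0.1924.
- Discordant cells: p10 = 0.30 − 0.1924 = 0.1076 and p01 = 0.35 − 0.1924 = 0.1576, sum 0.2652.
- Probability of a significant increase ≈ Φ{[(p01 − p10)√n − 1.96√(p10 + p01)] / √[p10 + p01 − (p01 − p10)²]}.
- n = 420: Φ[(1.0247 − 1.0094)/0.5125] = 0.51.
- n = 360: Φ[(0.9487 − 1.0094)/0.5125] = 0.45. Simulation gives 0.513 and 0.456.
- At least one of three video branches: 1 − (1 − 0.513)³ = 0.88.
- The same, with control (branch 1) not significant: 0.884 × (1 − 0.456) = 0.48.

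**4. The range, by simulation with correlation 0.4.**

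| Common change | Video branch (n=420) | Comparator branch (n=360) | At least one video branch | At least one video branch, control not |
| --- | --- | --- | --- | --- |
| none (30% to 30%) | 0.025 | 0.025 | 0.074 | 0.072 |
| 30% to 32% | 0.125 | 0.113 | 0.330 | 0.293 |
| 30% to 35% | 0.513 | 0.456 | 0.884 | 0.481 |
| 30% to 40% | 0.976 | 0.955 | >0.999 | 0.045 |
| 20% to 42% (pilot) | >0.999 | >0.999 | >0.999 | near 0 |

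In the last two rows the discordant pattern becomes rare because control is nearly always significant too. The criterion is then met in nearly every branch although no video has an effect.

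**5. The between-branch comparison under the same conditions.** With equal follow-up proportions of 25%, 30% or 42% in branches 1 and 5, a two-proportion test at 0.005 favours branch 5 in about 0.25% of simulated trials. Common change does not raise this rate.

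**The case against.** A reader might infer that the plan declares a branch effective on its own pre-post change. The documents do not say so. The criterion sentence does not use the term within-branch; that reading is an inference from the matching 0.05 level and the McNemar tests. The sentence before it refers to comparisons across branches, so significance of a between-branch difference in change is a possible reading. Evaluation of Branches measures efficacy against control and the text page. Between-branch regression is planned, as are logistic models with the pretest value and treatment status as predictors. All of this stands, and it limits the point to a badly stated criterion.

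A reader might also infer that Evaluation of Branches ranks branches by within-branch p-values. The phrase comes from a sentence comparing the videos with the text page, so only its wording is loose.

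It is also fair that common drift is not shown. Eligibility requires a recent new partner, but does not select on non-disclosure, no testing or no condom use, so regression to the mean on the primary outcomes does not follow directly. The only pre-post data come from a single-group pilot, in which alcohol use was 27% both times.

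On the other side, Appendix A takes that pilot's pre-post tests as strong support for effectiveness, and the sample-size section uses its baseline and follow-up testing rates (20% and 42%) as if they were control and intervention. The misreading is therefore a live one.

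**Conclusion.** The point holds as a defect in a stated rule, and it should be fixed. The minimal meaningful difference has no magnitude and no comparator, and it does not match the primary hypotheses or the power calculation. Applied branch by branch, it cannot separate a video effect from change common to all branches.

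The size depends on assumed drift. The 48% for a rise from 30% to 35% is not the trial's false-positive rate. It falls to about 29% for 30% to 32%, 7% with no drift, about 5% for 30% to 40%, and near 0% at the pilot's change. If branch 2 must also be non-significant, it is 0.884 × (1 − 0.456)² = 0.26. These figures use all men followed up; the HIV-test intention item goes only to men who are negative or untested, so a testing analysis limited to them would have smaller branches.

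A reader might compute 1 − 0.95^15 = 54% for 15 within-branch tests with no change at all. That figure counts declines and the comparator branches. For increases in the nine video-branch tests it is 1 − 0.975^9 = 20%, if the tests are independent. Neither figure is needed for the conclusion.

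**What to change.** - **Outcomes and Minimum Meaningful Differences.** Restate the minimal meaningful difference as a between-branch difference (a video branch versus branch 1 or 2), either in the baseline-adjusted follow-up outcome or in change from baseline. The sponsor should choose its size, for the binary outcomes from its own power table. Where disclosure is analysed as a Likert score, the size must be given on that scale.
- **Same section.** Delete "at both the 0.01 and 0.05 alpha levels" and use the between-branch alpha of Sampling, Sample Size, and Statistical Power.
- **Analysis of Treatment Branches.** State that efficacy conclusions rest on the between-branch contrasts already planned, reported with confidence intervals. State that McNemar results are supportive description and not evidence of efficacy.
- **Evaluation of Branches.** Replace "to determine which branch elicits the most significant change in behavior" with wording about the largest estimated difference versus the comparator.

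The cost is wording only, with no change to design, data collection or sample size. The downside for the sponsor is fewer nominally positive statements.

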**Training for Study Personnel**

No additional special training is necessary for this intervention project. The PI and co-investigators are trained in this type of research and have been conducting internet-based research for the past 5 years. No interviewers are needed. The PI will be the individual listed as the primary contact should a participant require additional information or have concerns with the study. The PI has specific experience in this regard.

**DATA HANDLING AND ANALYSIS**

Although no personally identifying information other than email addresses (which will be encrypted and stored separately), will be collected at any point during the surveys, several technical steps will be taken to ensure the security and privacy of data in general. All survey data will be stored on a secure Public Health Solutions web server with firewalls and industry standard protections and will be removed from the web server at the end of the survey period.

All analyses will be performed in SPSS 14.0 and SAS 9.1 for Windows. For the overall sample (3,000) we will use a reduced alpha level (.01) as a criterion for statistical significance. For the within-branch analyses (n=600 or less) we will use the conventional alpha level (.05). Due to decreased power, all interaction tests will be conducted at the 0.10 level of significance.

The first analytic procedure will be to use ANOVA or chi-square to compare key characteristics (i.e., age, race/ethnicity, income) among and between the 5 randomized groups to ensure that there are no statistical differences, and to verify that computerized randomization worked.

**Frequency Distributions**: Frequency distributions will be produced for all variables and be used to describe the sample characteristics and answer key questions (e.g., what percentage of men reported unprotected anal or vaginal intercourse in their last sexual encounter with a new male or female partner?).

**Bivariate Analysis:** Bivariate analysis will be conducted to identify measures that show significant associations with primary outcome variables, (e.g., asking or telling HIV status to new sex partners [yes/no], HIV testing during the 60 days after baseline [y/n], and unprotected anal or vaginal intercourse [y/n]). Associations between measures with more than two values (e.g., drug use increased, decreased, or remained the same) and binary outcomes (e.g., HIV/STI testing [y/n]) will be tested, though the Pearson Chi-Square test and t-tests will be performed with continuous variables (e.g., number of sex partners in past 60 days).

**Multivariate Analysis:** For dichotomous outcomes, we will use logistic regression models to simultaneously examine the effects of predictors found to have a statistically significant association with the binary outcomes in bivariate analyses. Further, logistic regression will allow the introduction of the pretest observation (e.g. asked new partner’s HIV status) and treatment status as predictors and a set of demographic control variables. For continuous outcomes, we will use linear regression models to study quantitative outcome variables such as number of days respondent drank alcohol in the past 60 days (at baseline and 60-day follow-up).

**Analysis of Treatment Branches:** For analysis of within-treatment branches, we will use McNemar’s Test, which is a chi-square test used when data consist of paired observations on a particular outcome (i.e., pre-post treatment design), such as HIV disclosure with a new sex partner. For analysis of between-treatment branches, we will test differences across interventions or group mean differences by employing linear regression with interaction terms. We will also use ANOVA to examine within- and across-branch differences between those who complete the intervention activities and those who do not.

**Safeguarding against Confounding:** To safeguard against confounding in the multivariate logistic regression models, variables not significantly associated with outcomes in simple bivariate analyses may be included for conventional demographic items or if it is highly plausible (either biologically or behaviorally) that they are associated with the outcome.

**Interactions:** Tests for interactions will be conducted between pairs of explanatory factors and binary outcomes to assess possible interactions.

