**Sampling, Sample Size, and Statistical Power**

The three primary outcomes in this study are increased HIV testing, HIV disclosure, and condom use. Using historical data from the pilot intervention (see Appendix A), we observed that HIV testing increased from 20% to 42% in HIV-negative men between baseline and 3-month follow-up. Based upon these values using a 2-group design (control vs. intervention), with a 5% significance level and 80% power, 77 participants would be required in each study condition for a total sample size of 154. In the current study, which has a 5 branch design, we anticipate that by enrolling 3,000 men and retaining 70% (N=2,111), we will have sufficient power to detect meaningful differences in behavior among the study branches.

Although we will be comparing within and across all study branches, we expect the greatest differences to be found between control branch 1 and branch 5 (both videos) for the primary outcomes. The Bonferroni correction will be used to protect the overall Type I error rate with multiple comparisons. In these comparisons, the nominal significance level will be set to alpha = 0.05 for two-sided tests (divided by the number of pairwise comparisons for individual tests). Using Chi-square tests to detect behavioral changes between the binomial primary outcomes, we obtain the following powers to detect a difference between two study branches for various true proportions and sample sizes (α=0.05; 10 pairwise comparisons).

| **Power Calculations for Meaningful Differences**  **between Study Branches** | | | | | |
| --- | --- | --- | --- | --- | --- |
| **Behavior Change Outcomes†** | | **Sample Size per Branch* and Associated Power** | | | |
| Branch A | Branch B | N = 300 | N = 400 | N = 500 | N = 600 |
| 0.10 | 0.15 | 0.142 | 0.221 | 0.308 | 0.396 |
| 0.10 | 0.20 | 0.709 | 0.865 | 0.944 | 0.979 |
| 0.10 | 0.25 | 0.978 | 0.997 | >.999 | >.999 |
| 0.15 | 0.20 | 0.097 | 0.150 | 0.210 | 0.275 |
| 0.15 | 0.25 | 0.569 | 0.747 | 0.863 | 0.931 |
| 0.15 | 0.30 | 0.939 | 0.988 | 0.998 | >.999 |
| 0.20 | 0.30 | 0.476 | 0.652 | 0.784 | 0.874 |
| 0.20 | 0.35 | 0.894 | 0.971 | 0.993 | 0.999 |
| 0.20 | 0.40 | 0.994 | >.999 | >.999 | >.999 |
| 0.30 | 0.40 | 0.375 | 0.536 | 0.673 | 0.780 |
| 0.30 | 0.45 | 0.821 | 0.936 | 0.980 | 0.994 |
| 0.30 | 0.50 | 0.984 | 0.998 | >.999 | >.999 |
| 0.40 | 0.50 | 0.336 | 0.488 | 0.623 | 0.733 |

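### The Bonferroni rule for the primary between-branch tests leaves out the three primary outcomes, and the analysis section adds unranked levels of 0.01 and 0.10

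*Protocol*

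**What the plan says.** **Sampling, Sample Size, and Statistical Power.** This section names HIV testing, HIV disclosure and condom use as the three primary outcomes. It promises that "The Bonferroni correction will be used to protect the overall Type I error rate with multiple comparisons". The power table is labelled "α=0.05; 10 pairwise comparisons", which gives 0.05/10 = 0.005 per test. A footnote says the table's outcomes are all three primary outcomes.

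**Specific Aims and Hypotheses.** The Aim 3 primary hypotheses list the three outcomes separately, ending with "condom use in intervention branches 3, 4, and 5, compared to branches 1 and 2". Neither this section nor any other says that all three must succeed.

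**Data Handling and Analysis.** Bonferroni is not mentioned here. The section states: "For the overall sample (3,000) we will use a reduced alpha level (.01) as a criterion for statistical significance". It gives 0.05 to within-branch analyses and then says: "Due to decreased power, all interaction tests will be conducted at the 0.10 level of significance". Under Analysis of Treatment Branches, for the between-branch analysis, "we will test differences across interventions or group mean differences by employing linear regression with interaction terms".

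**Outcomes and Minimum Meaningful Differences.** Change from baseline to follow-up in the primary outcomes is to be significant "at both the 0.01 and 0.05 alpha levels".

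**The concern.** There are two separate problems.

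1. **The family is too small for the promise.** Dividing by ten accounts for the branch pairs within one outcome. With three primary outcomes tested the same way, and success on any one open to being claimed, there are 30 tests. The overall error rate is then not held at 5%.

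2. **The governing level is not fixed.** The level used for power (0.005), the level for the overall sample (0.01) and the level for all interaction tests (0.10) can each be read onto the primary between-branch comparison, and nothing ranks them. A between-branch p-value of 0.007 fails at 0.005 but passes at 0.01. A p-value of 0.08 passes only at 0.10. The choice of rule could be made after the data are seen.

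**Working it through.** **Inputs from the protocol.** Five branches; three primary outcomes; two-sided 0.05 with ten pairwise comparisons; 600 enrolled per branch; expected attrition of 240 in branches 1 and 2 and of 180 in branches 3 to 5 (Attrition and Retention Efforts), so 360 and 420 completers.

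**Step 1. Reproduce the power table.** The ten pairs are 5 × 4 / 2 = 10, so alpha per test is 0.005 and z = 2.807. Power uses the two-proportion normal approximation with continuity correction:

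power = Φ{[d − ½(1/n₁ + 1/n₂) − z·SE₀] / SE₁}

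where d is the difference, SE₀ uses the pooled proportion and SE₁ the separate proportions. For 0.20 v 0.30 with 600 per branch:
- SE₀ = √(0.25 × 0.75 × 2/600) = 0.0250
- SE₁ = √[(0.16 + 0.21)/600] = 0.0248
- correction = 0.0017
- (0.1000 − 0.0017 − 0.0702)/0.0248 = 1.13, so power = 0.872, against 0.874 in the table

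All 52 cells agree within 1.3 percentage points at 0.005. Levels of 0.05, 0.01 and 0.05/30 do not reproduce the table. It is therefore sound for ten comparisons on one outcome.

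**Step 2. Familywise error at 0.005.** All ten pairwise z-tests were simulated with no true difference between branches.
- One outcome: about 4.0%, so the promise holds for a single outcome.
- Three independent outcomes: 1 − (1 − 0.040)³, about 11.6%.
- Bonferroni upper bound over 30 tests: 30 × 0.005 = 15%.

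**Step 3. If the 0.10 rule applied.** Suppose it governed one overall branch-by-time test per outcome. Error over three independent outcomes would be 1 − 0.90³ = 27.1%. Against the powered level, 0.10/0.005 = 20 times looser.

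**Step 4. A rule that covers the outcomes.** 10 pairs × 3 outcomes = 30 tests, and 0.05/30 = 0.00167 (z = 3.144). Simulated error over three independent outcomes with the expected completers is about 4.2%.

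**Step 5. What that costs.** Same power formula:

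| Comparison | n per branch | Power at 0.005 | Power at 0.00167 |
|---|---|---|---|
| 10% v 20% | 600 v 600 | 0.976 | 0.950 |
| 20% v 30% | 600 v 600 | 0.872 | 0.787 |
| 30% v 40% | 600 v 600 | 0.779 | 0.666 |
| 10% v 20% | 360 v 420 | 0.837 | 0.737 |
| 20% v 30% | 360 v 420 | 0.624 | 0.489 |
| 30% v 40% | 360 v 420 | 0.512 | 0.378 |

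For 20% v 30% with 360 v 420: SE₀ = 0.0313, SE₁ = 0.0307 and correction = 0.0026. At 0.00167 the argument is (0.1000 − 0.0026 − 0.0983)/0.0307 = −0.03, giving 0.489.

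**The case against.** The strongest reply is that different levels for different analyses are not a contradiction, and much of this stands.

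- **0.05.** A reader might infer that the between-branch comparison carries four levels, including 0.05. The text does not support that. Data Handling and Analysis assigns 0.05 to within-branch analyses, and the pair of levels under Outcomes and Minimum Meaningful Differences concerns change from baseline to follow-up. Neither is a clear between-branch rule.
- **0.10.** A reader might take it as settled that the primary test is run at 0.10. It is not. A separate Interactions paragraph deals with pairs of explanatory factors, and the stated reason, reduced power, suits tests of that kind. The between-branch regression's interaction terms are never identified, so branch-by-time is an interpretation. For binary outcomes the protocol also plans chi-square tests and logistic regression with treatment status as a predictor, and neither is an interaction test. The 0.10 sentence nevertheless says all interaction tests, and the between-branch analysis is described through interaction terms, so the ambiguity remains.
- **0.10 on each of the ten pairs.** This would give far larger error rates than 27%, but no section proposes it. The sample-size section puts the pairwise tests at 0.005.
- **The ten pairs.** A reader might object that four of them (1 v 2, 3 v 4, 3 v 5, 4 v 5) fall outside the primary hypotheses, and might want one pooled contrast of branches 3 to 5 against 1 and 2. But Evaluation of Branches makes comparison of the branches with one another a stated aim, and the hypothesis can be read pairwise. The protocol also expects its largest effect at branch 5 v 1. A pooled contrast tested at 0.05/3 would have power of only about 0.23 if branch 5 alone worked (30% v 20% elsewhere).

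None of this answers the omitted outcomes or the unranked 0.005 and 0.01.

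**Conclusion.** The protocol claims protection of the overall Type I error rate that its rule does not deliver. At 0.005 per test, error is about 4.0% for one outcome and about 11.6% across three. The 11.6% assumes independent outcomes, all ten pairs tested, and success on any one outcome counting. Positive correlation lowers it, and 15% is the ceiling.

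Separately, the text does not say whether 0.005 or 0.01 governs the between-branch tests, and on a literal reading it leaves 0.10 open as well. The 27% figure is conditional on that last reading and on a single overall test per outcome. This is a conflict within the protocol, not detail left to an analysis plan. The power table's arithmetic is not at fault; it answers the question for one outcome only.

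**What to change.** 1. State one multiplicity rule for the Aim 3 primary between-branch tests that covers all three outcomes. Bonferroni or Holm over the 30 tests would do (0.05/30 = 0.00167 for Bonferroni and for the first Holm step). A smaller prespecified family, adjusted across all three outcomes, would also do.
2. State that the 0.01 level for the overall sample does not govern these tests, and confine the 0.10 level to exploratory effect-modifier interactions.
3. Re-issue the power table at the level actually used, including the expected completers (360 and 420) as well as 600 per branch.

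The cost is protocol wording and a re-run table, with no new data. The downside is the loss of power shown above for the 30-test family: with the expected completers, 20% v 30% falls just below even odds of detection (0.49). A smaller family would recover some of that, at the price of leaving some of the stated branch comparisons outside the confirmatory set.
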